### Statistical and cost analysis

Baseline comparability will be investigated by descriptive statistics to examine if randomisation was successful. Differences in success rates between both groups are calculated, together with 95 per cent confidence intervals. In addition to an analysis of the difference in recovery between the two groups (as explained under the paragraph sample size) analyses of the difference in time to recovery will be carried out. Due to lack of data in the literature we could not base our sample size calculations on these differences. Survival-analysis is used to calculate differences in median time to recovery. Continuous outcomes are evaluated as change scores (differences between baseline measurement and each follow-up measurement). Multivariable analyses are performed to adjust for the eventual differences between the groups at baseline in prognostic indicators. All the analyses are performed according to the intent-to-treat principle. An additional per protocol analysis is performed comparing patients in the wait-and-see group who received surgery with patients in the same group who had not and with patients in the surgery group. To compare the actual treatment sec instead of strategies an explorative analysis will be performed in subgroups off all patients who actually received surgery and who did not receive surgery in both groups. All patients who withdraw from the study are included in the analysis until the time of withdrawal.

The result of this study will be a trade off between the disadvantages of surgery (hospitalisation, reduced quality of life and costs) versus the possible advantages (earlier relief of pain and return to work). For that reason recovery, measured as an 11 point difference in score when compared to baseline (Roland Disability Questionnaire for Sciatica), is the clinically most relevant patient outcome. Quality of Life (SF-36) and perceived recovery are important to compare the reduced quality of life from surgery to the possibly prolonged pain from conservative therapy and also to be able to compare cost-effectiveness with that of other spine interventions. The EuroQol is important to obtain cost-utility ratio's that can be compared with those of a wide range of other interventions. Utilities are obtained from the descriptive classification system of the EuroQol, using the model described by Dolan [43,53]. Conservative treatment may decrease costs compared to surgery but possibly at the expense of delayed effectiveness. In an incremental cost-effectiveness analysis, societal costs during the first year will be compared to the primary outcome measure (Roland Disability Questionnaire for Sciatica, averaged over the first year), Quality of Life (SF-36, during the first year) and perceived recovery (7-points Likert scale). Cost-effectiveness analyses with these effectiveness measures have been conducted before, allowing comparison with other spine interventions.

Finally, to answer the second research question explorative analyses are conducted to investigate whether the treatment effect after two, six and twelve months varies in specific subgroups of patients (Table 3).

**Table 3 T3:** Selected prognostic variables for subgroup analysis

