### Sample size

The result of this study is based on the short-term success of surgical intervention and will be a trade-off between a quicker relief of leg pain versus an advantage in cost-effectiveness for conservatively managed patients. The sample size is calculated on the basis of the Roland Disability Questionnaire for Sciatica averaged during the 12 months follow-up period. The numbers used for this sample-size are drawn from the Maine Lumbar Spine Study 1 year and recently published 5-year results [19,55]. The difference in the Roland score between the surgical- and non-surgical group in this study did not change between 3 and 12 months follow-up as shown in their study [19] and can be averaged over the first year. The main aim of this study is to measure the short-term functional difference at 12 months follow-up. Surgical treatment is considered better when the post treatment change is at least 4 points more when compared to the conservative treatment arm [38] and constant over time. Considering this constant difference and a mean standard deviation =10 over the first year [55] 140 patients per treatment arm are needed to reach a power (1-β) of 0,90 with α = 0.05 (two-sided). To answer the main research question 280 patients are needed for analysis with at least 12 months follow-up. The aim is to enrol 300 (150 per arm) patients in the study, including 8 % loss to follow-up after 1 year. The total number of operated patients each year in all participating hospitals exceeds 1400. With this number of patients also a clinically important difference in median time to recovery of two months can be detected by survival analysis. Although the time to recovery is the main issue, the problem of recurrent complaints is still not solved in the different approaches of survival and proportional hazard analysis.

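### The analysis section ties the sample size to the difference in recovery (an 11-point Roland response), but the size is justified only for a difference in mean Roland change; no power is established for recovery

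*Protocol article*

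**What the plan says.** The Sample size section names a continuous endpoint: "The sample size is calculated on the basis of the Roland Disability Questionnaire for Sciatica averaged during the 12 months follow-up period". The target effect is a difference in mean change: "Surgical treatment is considered better when the post treatment change is at least 4 points more when compared to the conservative treatment arm". The number follows from these: "Considering this constant difference and a mean standard deviation =10 over the first year [55] 140 patients per treatment arm are needed", for power 0.90 at a two-sided alpha of 0.05. The section has no recovery proportions, no responder difference and no 11-point rule. It mentions recovery only in connection with median time to recovery.

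The Statistical and cost analysis section first announces success rates: "Differences in success rates between both groups are calculated, together with 95 per cent confidence intervals". It then writes "In addition to an analysis of the difference in recovery between the two groups (as explained under the paragraph sample size") and contrasts that analysis with time to recovery, for which it says the literature gave no data on which to base a sample size.

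Recovery has a fixed meaning in the article. The Primary outcome measures section requires a Roland change from baseline of 11 points or more. The analysis section repeats the rule and, in the same sentence, gives this outcome the highest clinical relevance for patients: "For that reason recovery, measured as an 11 point difference in score when compared to baseline (Roland Disability Questionnaire for Sciatica), is the clinically most". The Primary outcome measures section also names the Roland questionnaire itself as the main primary outcome.

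**The concern.** The cross-reference sends the reader to a calculation for a different quantity. A difference in means and a difference in the proportion passing a cut-off are different comparisons, and the power of one does not carry over to the other. Read with the article's own definition, the sentence makes the yes/no recovery comparison the one that the sample size supports.

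One instrument then has two candidates for the deciding analysis: the mean Roland change, with a stated power, and 11-point recovery, with none but with the label of greatest clinical relevance. If the two disagree, the text does not say clearly which one the trial was designed to answer. The Background links the result to whether guidelines on the timing of surgery should change. A non-significant difference in recovery, wrongly credited with 90% power, could therefore be taken as support for waiting.

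**Working it through.** **1. The plan's own figure.** Inputs from the Sample size section: difference δ = 4, SD σ = 10, two-sided α = 0.05, power 0.90.

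n per arm = 2(z₀.₉₇₅ + z₀.₉₀)² σ²/δ² = 2 × (1.960 + 1.282)² × 100/16 ≈ 131.3, so 132.

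Power at 140 per arm: standard error = 10 × √(2/140) = 1.195; 4/1.195 − 1.960 = 1.387; Φ(1.387) = 91.7%. The t-test version gives 91.5%. The stated 140 is sound, and slightly generous, for the mean comparison.

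**2. What that implies for recovery.** The article gives no recovery rate for either arm, so nothing follows without an assumption about the distribution of change scores. Any figure from here on is an illustration.

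**3. Normal illustration.** Assume change is N(m, 10²) in the conservative arm and N(m + 4, 10²) in the surgical arm, with recovery meaning change ≥ 11. Then p₀ = 1 − Φ((11 − m)/10) and p₁ = 1 − Φ((7 − m)/10). Power is for the two-proportion z-test with pooled null variance, 140 per arm.

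| m | p₀ | p₁ | power |
|---|---|---|---|
| 0 | 13.6% | 24.2% | 62.4% |
| 3 | 21.2% | 34.5% | 70.0% |
| 9 | 42.1% | 57.9% | 75.8% |
| 15 | 65.5% | 78.8% | 70.0% |
| 20 | 81.6% | 90.3% | 55.7% |

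The peak row in full: difference 0.1585; null standard error √(2 × 0.25/140) = 0.0598; alternative standard error √((0.421 × 0.579 + 0.579 × 0.421)/140) = 0.0590; (0.1585 − 1.960 × 0.0598)/0.0590 = 0.70; Φ = 75.8%. With unpooled variance it is 76.6%. If all 150 enrolled per arm are analysed, the peak is 78.7% (79.4% unpooled). Under this model, 90% power in the best case needs 207 per arm.

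**4. Does the shape matter?** The Roland score runs from 0 to 23, so its SD cannot exceed 11.5, and an SD of 10 is close to that limit. In the peak row the surgical mean is 13, and the normal model puts 1 − Φ(1) ≈ 16% of surgical patients above an improvement of 23 points, which is impossible. Bounded alternatives, again with a 4-point difference and 140 per arm:

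- Two possible changes 20 points apart on either side of the cut-off, 40% v 60% recovered (mean difference 0.20 × 20 = 4; SD 20 × √(0.4 × 0.6) = 9.8): 92%.
- Beta-distributed change on 0 to 23, SD 10: about 84–88%.
- Beta-distributed change on −6 to 17, SD 10: 53–98%, depending on the mean.

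**5. What recovery would need.** At 140 per arm, 90% power requires a difference in recovery of about 19 percentage points when the control rate is 30–50% (18.8, 19.3 and 18.9 points at 30%, 40% and 50%). The article states no such assumption.

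**The case against.** The strongest reply is that recovery in the disputed sentence is loose wording for the Roland change. The Sample size section explains only one between-group analysis with a calculated size, the sentence contrasts it with time to recovery, and success rates have their own earlier sentence. On this reading there is no power problem, only inconsistent terminology. The reading is possible, but it conflicts with the 11-point definition, which is given twice, once in the same analysis section. Even if it is accepted, one word names both a mean change and a responder status, and the sentence still needs correcting.

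Much of the right framework is already present: the Roland is the main primary outcome, continuous outcomes are analysed as change scores, and success rates come with confidence intervals. That stands, and it is why the repair is small.

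Three stronger readings are tempting, and the documents do not support them:

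- *The protocol claims 90% power for recovery.* No section says so. The cross-reference only implies that the calculation covers recovery.
- *Recovery has at most 76% power, so a type II error of at least 24%, and needs 207 per arm.* These figures hold only for normal change scores. Bounded shapes give lower and higher power, including above 90%.
- *The plan treats a non-significant recovery difference as equivalence.* No such rule is stated. Over-reading is a risk of the wording, not a planned analysis.

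**Conclusion.** The point holds as a mismatch between two sections. The sample size is justified for a 4-point difference in mean Roland change, and correctly so, but the analysis section attributes that justification to the difference in recovery. With no recovery rates given, power for the 11-point comparison is unknown. It is about 76% at best if change scores are normal with the protocol's SD and difference. Across the bounded shapes tried above it runs from 53% to 98%. The trial is not shown to be too small; what lacks support is reading the stated 90% as applying to recovery.

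**What to change.** In Statistical and cost analysis, replace the cross-reference, for example with: *The main between-group analysis is the difference in mean Roland change averaged over the first 12 months; the sample size and its 90% power refer to this analysis. The proportion with a Roland change of 11 points or more is a supporting responder analysis, reported as a difference with its 95% confidence interval. The sample size was not based on it, and a non-significant difference is not evidence of equal effect.*

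This agrees with the Sample size section and with the naming of the Roland as the main primary outcome. No power for recovery need be quoted. If one is, state the assumed recovery rate in each arm and show a range; the normal-model figure should not go in on its own.

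The cost is a wording change in one section and no extra patients. The small downside is that recovery, still described as the most clinically relevant outcome, can no longer be presented as the powered comparison.

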### Treatment allocation

Patients will randomly be allocated to either surgery within 1–2 weeks or prolonged conservative treatment by their GP. Patients, their doctors and research nurses can obviously not be blinded for the allocated treatment. Blinding of the outcome measurements is not possible, due to the fact that mainly self-reported outcomes are used. A randomization list is prepared for every participating hospital. Permuted blocks of random number patients are formed to ensure near-equal distribution of patients over the two randomization arms in the hospitals. Using random number tables generates the random sequence of the permuted blocks. The data manager, who is not involved in the selection and allocation of patients will prepare coded, sealed envelopes containing the treatment allocation. During the second patient visit the research nurse will open the envelope together with the patient and appointments will be made for the allocated treatment, either surgery or referral back to the GP, to ensure that treatment is started as soon as possible after randomization. This will be done after checking all the criteria and especially the persistence of pain with disability in daily functioning. A letter about the allocated treatment arm informs all caregivers. Although the principal investigator will not include and operate upon trial patients he may be biased with a preference for surgery, which could theoretically influence analysis. Therefore the principal investigator is blinded for the allocated treatment. As he is not involved in treatment of the study population blinding during later analysis is only possible after blinding during the randomization and follow-up period.

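### Analysing RDQ as raw per-visit change, with adjustment only for baseline differences that turn up, gives up precision, leaves the covariates open and does not match the year-averaged RDQ of the sample size

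*Protocol article*

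**What the plan says.** Statistical and cost analysis, in the protocol article, sets the method for every continuous outcome: "Continuous outcomes are evaluated as change scores (differences between baseline measurement and each follow-up measurement". The next sentence brings in covariates: "Multivariable analyses are performed to adjust for the eventual differences between the groups at baseline in prognostic indicators". No covariate is named for the main comparison. A descriptive check of baseline comparability comes first in the same paragraph.

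The Sample size section works with a different quantity: "The sample size is calculated on the basis of the Roland Disability Questionnaire for Sciatica averaged during the 12 months follow-up period". The cost-effectiveness part of the analysis section also uses RDQ averaged over the first year. The planning inputs are a target, "Surgical treatment is considered better when the post treatment change is at least 4 points more when compared to the conservative treatment arm", and a spread, "a mean standard deviation =10 over the first year". The section does not say whether that SD belongs to the score or to its change. The result is "140 patients per treatment arm are needed to reach a power (1-β) of 0,90 with α = 0.05 (two-sided".

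Two further statements bear on the point. Under Treatment allocation: "A randomization list is prepared for every participating hospital". Under Statistical and cost analysis: "All patients who withdraw from the study are included in the analysis until the time of withdrawal".

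**The concern.** There are three linked weaknesses.

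- **Precision.** Subtracting the baseline score in full is the best use of it only in a special case. Adjusting for it by regression (ANCOVA) is never less precise in large samples and is usually more so. Baseline RDQ is collected anyway, so the loss is avoidable.
- **Covariates.** Adjusting for differences that happen to appear makes the model depend on the observed data. Table 3 alone offers 18 candidate variables (2+10+4+2), and those are listed for subgroup analysis. The article does not say which answer counts if adjusted and unadjusted results differ.
- **Estimand.** A series of changes, one per visit, is not the year-averaged RDQ on which the trial was sized.

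At stake are the standard error of the main comparison and a clear statement, made in advance, of which RDQ result answers the main question.

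**Working it through.** **Inputs from the Sample size section.** Difference 4 points, SD 10, two-sided α 0.05, power 0.90, 140 per arm. The correlation ρ between baseline and follow-up RDQ is not given. I assume 0.2 to 0.7.

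**The plan's own figure.** n per arm = 2(1.960+1.282)²·10²/4² = 131.3, so 132 against the stated 140. With 140 per arm the standard error is 10·√(2/140) = 1.195, and power = Φ(4/1.195 − 1.960) = 0.917. The stated size is slightly conservative and its power claim holds on its own inputs.

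**Variances.** Let s be the SD of the score, equal at baseline and follow-up.

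- Raw change: 2s²(1−ρ)
- ANCOVA: s²(1−ρ²)
- Ratio, ANCOVA to change: (1−ρ²)/[2(1−ρ)] = (1+ρ)/2

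**Two readings of SD 10**, for 4 points and 140 per arm:

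- (a) 10 is the SD of change. Raw change then has power 0.917 whatever ρ is, and the ANCOVA SD is 10·√((1+ρ)/2).
- (b) 10 is the SD of the score. The change SD is 10·√(2(1−ρ)) and the ANCOVA SD is 10·√(1−ρ²).

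| ρ | Ratio | (a) ANCOVA SD | (a) ANCOVA power | (b) change SD | (b) change power | (b) ANCOVA SD | (b) ANCOVA power |
|---|---|---|---|---|---|---|---|
| 0.2 | 0.60 | 7.75 | 0.991 | 12.65 | 0.754 | 9.80 | 0.927 |
| 0.3 | 0.65 | 8.06 | 0.986 | 11.83 | 0.807 | 9.54 | 0.939 |
| 0.4 | 0.70 | 8.37 | 0.979 | 10.95 | 0.863 | 9.17 | 0.955 |
| 0.5 | 0.75 | 8.66 | 0.972 | 10.00 | 0.917 | 8.66 | 0.972 |
| 0.7 | 0.85 | 9.22 | 0.953 | 7.75 | 0.991 | 7.14 | 0.997 |

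Under (a), the number per arm for 90% power falls from 132 to between 79 (ρ 0.2) and 112 (ρ 0.7). Under (b), raw change misses 90% at ρ 0.4 and below and exceeds it from ρ 0.5.

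**Unequal spread.** Let k be the baseline SD divided by the follow-up SD. The ratio of change to ANCOVA variance is then 1 + (k−ρ)²/(1−ρ²).

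| k (assumed) | ρ 0.2 | ρ 0.3 | ρ 0.5 |
|---|---|---|---|
| 1 | 1.67 | 1.54 | 1.33 |
| 0.75 | 1.32 | 1.22 | 1.08 |
| 0.5 | 1.09 | 1.04 | 1.00 |

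Patients are selected for severe disabling leg pain (Table 1), which may narrow the baseline spread, so k below 1 is plausible. The ratio never drops below 1. The same formulas serve the year average if k and ρ are taken for that average.

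**The case against.** The best defence is that the quoted sentence says how outcomes are expressed and does not exclude baseline RDQ from the multivariable model. If baseline RDQ were in that model, change and follow-up score would give the same treatment estimate: moving the baseline term across the equation alters only its own coefficient. The loss would then vanish. This is correct, but the text ties adjustment to differences seen between the groups, so on its wording baseline RDQ enters only if it happens to differ.

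It is also fair that the plan is not underpowered on every reading. If SD 10 is the SD of change, the planned 4 points already have power 0.917, and only extra precision is forgone. And no significance test triggers the adjustment, since the baseline comparison is descriptive. That softens the covariate point without removing it.

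Three stronger readings are tempting, and the document does not support them.

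- **Hospital is ignored in the analysis.** Lists are prepared per hospital, but the article does not say whether hospital enters the models, and a condensed article may leave that to the full plan. Omission would matter little. With an assumed 1% to 10% of variance between hospitals, including hospital moves power from 0.917 to 0.920–0.942. Leaving it out gives a type I error of about 0.049–0.039, slightly conservative.
- **Withdrawal handling breaks intention-to-treat.** Keeping patients in their arm up to withdrawal is ordinary censoring for the survival analysis, and a longitudinal model uses the same data. In separate per-visit analyses withdrawn patients are absent from later visits, but the article does not exclude them from the trial analysis.
- **The result is biased.** Raw change is unbiased under randomisation. Differential withdrawal is possible in an unblinded trial, but the article foresees only 8% loss overall and says nothing of a difference between arms.

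**Conclusion.** The point holds as one of efficiency and prespecification, not of validity. As worded, the plan analyses RDQ less precisely than its own data allow, leaves the covariates to observed imbalance, and does not tie the per-visit changes to the year-averaged measure behind the sample size.

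With equal variances, baseline adjustment removes 15% to 40% of the variance for ρ of 0.7 to 0.2. For 4 points with 140 per arm, that means power of about 0.95–0.99 instead of 0.917 if SD 10 is the SD of change. If it is the SD of the score, raw change falls short of the promised 0.90 at ρ 0.2–0.4 (0.75–0.86), where adjustment gives at least 0.927.

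These figures rest on assumed ρ, on equal spread at baseline and follow-up, and on a reading of the SD that the article leaves open. With a narrower baseline spread the gain can be close to nil. The direction does not depend on these assumptions: adjustment is not less precise in large samples.

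**What to change.** Replace the change-score sentence, for RDQ, with one longitudinal model over the visits at 2, 4, 8, 12, 26, 38 and 52 weeks. Its terms are baseline RDQ by visit, arm, visit and arm by visit, and it uses all available follow-up of randomised patients.

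Then state in advance:

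- the primary contrast from that model, either the year average (with the weights of the visits, which are unevenly spaced) or the 12-month difference;
- which pre-treatment RDQ is the baseline, since Table 2 marks RDQ at week 0 and in the column before it;
- any further covariates, by name, in place of adjustment for observed differences;
- whether SD 10 refers to the score or to its change.

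Hospital can be added to this linear model as a sensible term, because it is the randomisation stratum. I would not carry it over automatically to logistic models: 300 patients in 15 hospitals average 20 each, so strata may be sparse.

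The cost is revised wording, some programming and reliance on a missing-at-random assumption, which should be stated. No extra patients, visits or measurements are needed.
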